## Abstract

**Background:**

Clinical guidelines recommend specific targets for low-density lipoprotein cholesterol (LDL-C) and non-high-density lipoprotein cholesterol (non-HDL-C) for primary prevention of cardiovascular disease (CVD). Furthermore, individual variability in lipid response to statin therapy requires assessment of the association in diverse populations.

**Aim:**

To assess whether lower concentrations of LDL-C and non-HDL-C are associated with a reduced risk of major adverse cardiovascular events (MACE) in primary prevention of CVD.

**Design & setting:**

An international, new-user, cohort study will be undertaken. It will use data from three electronic health record databases from three global regions: Clinical Practice Research Datalink, UK; PREDICT-CVD, New Zealand (NZ); and the Clinical Data and Analysis Reporting System, Hong Kong (HK).

**Method:**

New statin users without a history of atherosclerotic CVD, heart failure, or chronic kidney disease, with baseline and follow-up lipid levels will be eligible for inclusion. Patients will be classified according to LDL-C (<1.4, 1.4–1.7, 1.8–2.5, and ≥2.6 mmol/l) and non-HDL-C (<2.2, 2.2–2.5, 2.6–3.3, and ≥3.4 mmol/l) concentrations 24 months after initiating statin therapy. The primary outcome of interest is MACE, defined as the first occurrence of coronary heart disease, stroke, or cardiovascular death. Secondary outcomes include all-cause mortality and the individual components of MACE. Sensitivity analyses will be conducted using lipid levels at 3 and 12 months after starting statin therapy.

**Conclusion:**

Results will inform clinicians about the benefits of achieving guideline recommended concentrations of LDL-C for primary prevention of CVD.

## How this fits in

To the authors’ knowledge, this is the first international study to assess LDL-C concentrations after initiating statin therapy for primary prevention of CVD in real-world populations. This extends the evidence obtained from randomised clinical trials. Results will inform patients and clinicians about the associated benefits of guideline recommended LDL-C and non-HDL-C targets in real-world practice.

## Introduction

CVD is the leading cause of death globally.^1^ Atherogenic lipoproteins (LDL-C and non-HDL-C) are well-established risk factors for atherosclerotic CVD.^2,3^ Recent evidence from secondary prevention trials indicates that individuals with lower LDL-C concentrations have a reduced risk of subsequent cardiovascular events.^4,5^

While lower targets for LDL-C are gaining wider acceptance for secondary prevention of CVD, there remains limited evidence for specific lipid targets for primary prevention. The recent European clinical guidelines for the treatment of dyslipidaemia emphasise specific LDL-C and non-HDL-C targets for primary prevention according to level of CVD risk.^6^ However, whether achieving a specific lipid target while taking statin therapy for primary prevention corresponds to a reduction in cardiovascular events is uncertain, as most randomised controlled trials of statin therapy have not allocated patients to specific lipid targets. It is also unknown whether there is a lipid level threshold, below which no added clinical benefit is obtained, and if a 'lower is better' approach is appropriate for primary prevention of CVD. Understanding the lowest absolute beneficial level of LDL-C is important as very-low LDL-C levels are now achievable with proprotein convertase subtilisin-kexin type nine inhibitors, and emerging treatments such as inclisiran.^4,7^ The association between on-treatment cholesterol levels and risk of cardiovascular events has been assessed, but these have mostly been in secondary prevention statin trials, and whether these findings extend to clinical practice marked by individual variability in statin response requires further investigation.^8^

Ethnic group, and consequently pharmacogenomics, influences response to statin therapy, particularly for Asians.^9^ Variability in statin response may be present for other non-Caucasian ethnic groups. Moreover, organisation of health systems,^10^ statin dosing,^11^ and individual response to treatment^12^ vary and may impact the magnitude of benefit derived from statin therapy. Given these factors, an assessment of lipid levels in diverse populations is needed to provide representative data, as most primary prevention statin trials enrolled middle-aged Caucasians.^13^ Therefore, this study has two objectives:

To compare the incidence of MACE in adults taking statins for primary prevention of CVD between HK, NZ, and the UK; andTo assess the association between LDL-C and non-HDL-C concentrations at 24 months after initiating statin therapy and MACE in adults taking statins for primary prevention of CVD, across three geographically and ethnically diverse populations.

The findings will be relevant to clinicians and organisations developing treatment guidelines worldwide.

## Method

### Study design

An international, multiple database study will be conducted, using a distributed network approach. Each site will follow a common protocol, to conduct an exposure-based new-user cohort study. The overall study design, study population, criteria for inclusion and exclusion, and follow-up time are shown in Figure 1. The cohort entry date (index date) is defined as the first dispensing or prescribing of a statin between 1 January 2007 and 31 December 2012. To prevent survival bias and covariate measurement bias, a new user, rather than a prevalent user, design will be used. A new statin user is defined as a patient who initiates a statin and received no lipid-modifying therapy prior to the cohort entry date. This protocol is written in accordance with the REporting of studies Conducted using Observational Routinely collected health Data for PharmacoEpidemiology statement (RECORD-PE).^14^

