### Outcomes and follow-up

The primary outcome of interest is MACE, defined as a diagnosis of either coronary heart disease, stroke, or cardiovascular death. Secondary outcomes include all-cause mortality and the individual components of the composite MACE outcome. Follow-up will begin after the end of the exposure assessment window (24 months after prescribing or dispensing of the first statin prescription) and will end at the earliest of outcome of interest, death, disenrollment or transfer from primary care practice, or end of the analysis period (31 December 2017).

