#### Statistical analysis

Descriptive statistics will be used to characterise the study population. Continuous variables will be summarised using mean and standard deviation or median and interquartile range, and categorical variables will be expressed as frequency and percentage. The crude incidence rates for the outcomes of interest will be estimated, reported as cases per 1000 person years with 95% confidence intervals (CIs) derived from a Poisson or negative binomial distribution as appropriate. Time-to-event analysis using Cox proportional hazards models will be used to estimate hazard ratios with 95% CIs. The proportional hazards assumption of the Cox model will be assessed. Potential confounders will be pre-specified based on expert knowledge and available literature, and adjusted for in the model. Using the common protocol, each analysis will be run locally. Estimates for each of the three sites will then be pooled by meta-analysis using a random effects model, and heterogeneity will be estimated using *I*
^2^. All statistical analyses will be performed using either Stata, SAS, or R software.

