#### Covariates

Each site will define covariates that are appropriate in the context of their electronic health record database. A pre-specified minimum list of potential confounders will be adjusted for. Exploratory modelling will include adjusting for additional confounders that may be available in specific databases.

The confounders to be adjusted for in each database are as follows:

Age on index dateSexDiagnosis of hypertensionDiagnosis of atrial fibrillationDiagnosis of diabetesDiagnosis of dyslipidaemiaDiagnosis of obesitySmoking status, or prescription for nicotine replacement therapy or diagnosis of chronic obstructive pulmonary disease (COPD)Alcohol use (where available) or diagnosis of chronic liver diseaseDiagnosis of rheumatoid arthritis or systemic lupus erythematosusDiagnosis of mental illness (for example, depression, anxiety, bipolar, and/or schizophrenia)Prescription for any antihypertensive medication (for example, angiotensin converting enzyme inhibitors, angiotensin II receptor blockers, calcium channel blocker, beta-blocker, and/or diuretic)Prescription for antidiabetic drugPrescription for antiplatelet agentsPrescription for oral anticoagulants.

Additional confounders that may be adjusted for subject to data source availability:

Deprivation indexBaseline systolic and diastolic blood pressureBaseline body mass indexFamily history of CVD.

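### Calendar year of statin start is in neither adjustment list although entry spans six years; adding it is a free improvement against a probably small confounder

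*Protocol article*

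**What the plan says.** - **Entry.** Study design sets the index date as the "first dispensing or prescribing of a statin between 1 January 2007 and 31 December 2012", which is six calendar years.
- **Follow-up.** Outcomes and follow-up starts the clock "24 months after prescribing or dispensing of the first statin prescription", so between 2009 and the end of 2014. It stops for all patients on 31 December 2017 at the latest.
- **Model.** Under Statistical analysis: "Time-to-event analysis using Cox proportional hazards models will be used to estimate hazard ratios with 95% CIs". Models are run locally and the three site estimates are pooled by random-effects meta-analysis. Stratification of the baseline hazard is not mentioned.
- **Compulsory confounders.** Covariates states: "The confounders to be adjusted for in each database are as follows". Fifteen items follow, beginning with age on index date and sex. None is calendar or index year.
- **Optional confounders.** Under "Additional confounders that may be adjusted for subject to data source availability" come deprivation index, blood pressure, body mass index and family history of CVD. Index year is absent here too.
- **Status of the list.** "A pre-specified minimum list of potential confounders will be adjusted for" Beyond that, "Exploratory modelling will include adjusting for additional confounders that may be available in specific databases".
- **Other analyses.** Neither the subgroup nor the sensitivity analyses use calendar year.

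**The concern.** Follow-up begins at the 24-month landmark, so the natural Cox time axis is time since that landmark (the article does not name the axis). On that axis, the risk set at two years holds 2007 starters observed in 2011 and 2012 starters observed in 2016. Any difference between entry years in both the chance of a low attained LDL-C and the MACE hazard then passes into the hazard ratio. Age on index date does not stand in for calendar year. Statin dose intensity is planned only as a subgroup variable, so a shift in intensity over time would not be absorbed by adjustment either.

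What is at stake is the contrast between the LDL-C and non-HDL-C groups. A bias of this kind does not shrink with more patients. The omission also cannot be put down to condensing for publication, because the article prints its pre-specified list item by item.

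**Working it through.** **1. The plan's own event figure.** From Feasibility assessment and sample size: 140 000 patients × 3 years × 10/1000 = 4200 events in CDARS. This matches the stated figure. It uses one flat rate, with no change by calendar year.

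**2. Entry year and possible follow-up.** For a mid-year starter, maximum follow-up is 2018 − (entry year + 0.5 + 2):

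| Entry year | 2007 | 2008 | 2009 | 2010 | 2011 | 2012 |
|---|---|---|---|---|---|---|
| Years | 8.5 | 7.5 | 6.5 | 5.5 | 4.5 | 3.5 |

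Entry years therefore contribute unequally to the risk sets, and a bias calculation has to allow for this.

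**3. Bias from omitting index year.** Assumptions, none of them from the documents: true hazard ratio 1.00, six equal entry cohorts, censoring at the end of 2017, and a hazard of about 1% a year that changes by a constant factor per entry year. At time t, let n1 and n0 be the numbers at risk in the low-LDL-C group and the rest, and d1 and d0 their expected events, each summed over entry years. The large-sample Cox estimate is the b that solves

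Σ over t of [ d1 − (d1 + d0) · n1·e^b / (n1·e^b + n0) ] = 0.

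Results for e^b at 10% exposure prevalence:

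| Odds of low-LDL-C group, per entry year | MACE hazard, per entry year | Apparent HR |
|---|---|---|
| +3% | −2% | 0.9987 |
| +5% | −2% | 0.9978 |
| +10% | −5% | 0.9891 |
| +20% | −7% | 0.9705 |

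At 30% prevalence the values are almost the same (0.9987 and 0.9711 at the two ends).

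**4. A rarer lowest group.** Suppose instead that the share below 1.4 mmol/l rises linearly over the entry years:

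- 3% to 6%, hazard −2% a year: 0.993. As a fraction of the planned effect, ln 0.9934 / ln 0.85 = 0.0066/0.1625 = 4%.
- 2% to 8%, hazard −5% a year: 0.968, and ln 0.968 / ln 0.85 = 0.0325/0.1625 = 20%.

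A simple ratio of mean hazards, weighting entry years equally, gives 0.992 and 0.962 for the same two cases (5% and 24%). It overstates the bias because it ignores the shorter follow-up of late entrants.

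**5. Direction.** With the attainment trend reversed and the MACE trend unchanged, the first and last rows of the table in step 3 become 1.0013 and 1.0274. The sign depends on the two trends.

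**The case against.** **The mechanism is assumed.** Confounding by calendar year needs a trend in attained lipids and a trend in MACE within the same database, and the documents report neither. The targets come from guidelines that the Introduction calls recent, and nothing shows that attainment below 1.4 mmol/l rose among 2007–2012 starters. This stands, and it limits the point to a conditional one.

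**The size is small.** The 20% figure needs the share below 1.4 mmol/l to quadruple while MACE falls 5% a year. The calculation also adjusts for nothing else, so any part of a trend carried by listed covariates such as diabetes or antihypertensive use would already be removed. This stands too.

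**The list is a minimum.** Nothing bars a site from adding index year. That is true, but the additions foreseen are exploratory and database-specific, whereas index date exists at every site. If only some sites added it, the pooled estimates would rest on different adjustment sets.

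**Stronger readings.** A reader might infer that the low-LDL-C groups will look better than they should, that outcome coding drifted, or that trends differ by country and so inflate between-site heterogeneity. The documents support none of these. Fitting the model within each site already keeps differences in level between countries out of the hazard ratio, and the article anticipates heterogeneity and estimates it with I².

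**Conclusion.** The omission is a fact of the text: six entry years, two printed lists without index year, and no stratification by it. That it biases the results is not established. If attainment rose and MACE fell over entry years, a true hazard ratio of 1.00 would appear as about 0.999 to 0.97 over the trends tried, with almost no bias at the mild end. Other trends would change the size or the sign. The result also assumes time since the landmark as the Cox time axis. This is a minor point and a free improvement. It is neither an error in a figure nor a contradiction, and it does not threaten the design.

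**What to change.** In Covariates, add calendar year of index date (six categories or a spline) to the compulsory list for all three sites. Alternatively, state under Statistical analysis that each site's Cox model is stratified by index year. Apply the same choice to the 3-month and 12-month sensitivity analyses.

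Cost: at most five degrees of freedom per site, against about 4200 expected events in CDARS alone. It needs no new data and loses no patients, because the index date defines cohort entry and is held for everyone. Since each site runs its analysis locally, the term should be written into the common protocol before the models are run.

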**Figure 1. fig1:**
[figure not shown]
Cohort study restricted to new users of statins for primary prevention of cardiovascular disease. Figure adapted from www.repeatinitiative.org.
^25^
^a^Defined as total cholesterol, low-density lipoprotein cholesterol, and high-density lipoprotein cholesterol. ^b^For example, body mass index, blood pressure, and deprivation index. ^c^Censored at earliest of MACE, death, disenrollment, or end of the study period. CVD = cardiovascular disease. LDL-C = low-density lipoprotein cholesterol. MACE = major adverse cardiovascular event. non-HDL-C = non–high-density lipoprotein cholesterol. Rx = prescription.

### Setting and data sources

Patient data will be included from electronic health record databases in three different countries. The Clinical Practice Research Datalink (CPRD) GOLD (UK) and PREDICT-CVD (NZ) are primary care databases; the Clinical Data and Analysis Reporting System (CDARS) (HK) is an integrated health system database (primary and hospital care).

CPRD contains anonymised patient data for >15 million patients and is representative of the general UK population in terms of sex, age, and ethnic group. CPRD is one of the largest quality-assured databases of longitudinal medical records from primary care in the world, with approximately 700 UK primary medical care practices (that is, covering approximately 10% of the UK population). CPRD has good ascertainment of major diagnoses, has been validated for pharmacoepidemiology studies, and has a long-established use for major research.^15^

PREDICT-CVD is a prospectively designed, open-cohort study in NZ that automatically recruits participants when primary healthcare practitioners complete standardised CVD risk assessments using PREDICT decision-support software.^16^ Approximately 95% of New Zealanders are enrolled in primary health organisations, which provide the majority of primary health care to New Zealanders nationally.^17^ About a third of the country's population is served by clinics that use PREDICT software, mainly in the Auckland and Northland regions of NZ. Participant risk factor profiles captured by the software are regularly linked to national databases documenting drug dispensing and International Classification of Diseases (ICD)-coded hospitalisations and deaths related to CVD. Data linkage from PREDICT-CVD will be performed using data of hospitalisations and emergency department (ED) visits drawn from the National Minimum Dataset (NMDS), and data from the Integrated Data Infrastructure (IDI), as well as the Mortality, National Lab Monitoring, Pharmaceutical collections (that is, record of dispensed medication based on claims data), from the Ministry of Health NZ and Testsafe databases (containing dispensing data for the northern NZ region). These health datasets contain data from different parts of the health sector, obtained from patient utilisation of health services, mandatory reporting national collections, or national population health surveys.

CDARS contains electronic health record data from the Hong Kong Hospital Authority, an integrated public healthcare system, which serves >7.4 million HK residents through 43 hospitals and institutions, 49 specialist outpatient clinics, and 73 general outpatient clinics.^18^ CDARS covers approximately 80% of all hospital admissions in HK,^19^ and has been extensively used for conducting high-quality population-based studies. Data validation has demonstrated a high-coding accuracy in CDARS.^20^

### Feasibility assessment and sample size

At the time of submission, access to the study cohorts from CDARS and CPRD has been obtained, and an application for access to PREDICT-CVD data has been submitted.

Initial assessment of the CDARS cohort of new statin users without a history of atherosclerotic CVD identified 267 243 patients. After application of all eligibility criteria, it is expected to include approximately 140 000 patients, who will have at least 3 years of follow-up after the exposure assessment window. Assuming an incidence of 10 per 1000 person years for the outcome of MACE, an estimated 4200 outcome events will be observed in the CDARS cohort. The authors' previous study using CPRD, included 165 411 patients and identified 22 798 CVD events.^12^ After pooling the three cohorts, the number of patients and events is sufficient for a two-sided significance level of 0.05, power of 0.80, and planned hazard ratio of 0.85 (see Supplementary Appendix S1).^2,21^

### Eligibility criteria

To be included in the study, each patient must meet the following eligibility criteria:

Have at least one documented baseline lipid test for total cholesterol (TC), HDL-C, and LDL-C within a year prior to index date.Have at least 12 months of clinical records after registration at the practice site (CPRD) or in the database (PREDICT).Have no previous history of atherosclerotic CVD:defined as a hospital or outpatient diagnosis of coronary heart disease (for example, myocardial infarction, ischaemic heart disease, angina, coronary artery bypass graft, percutaneous intervention), cerebrovascular disease (stroke or transient ischaemic attack), or peripheral artery disease (PAD), prior to index date; ordiagnosis of heart failure, chronic kidney disease, or diabetes with chronic kidney disease, due to their equivalent level of risk as people with established CVD, prior to index date; ora prescribing or dispensing of at least one prescription for nitrates, other antianginal drugs, peripheral vasodilators, loop diuretics, or metolazone within a year prior to index date.Be aged ≥18 years on index date.Have at least two additional statin prescriptions 1 year following index date.Have at least one documented follow-up lipid test for TC, HDL-C, and LDL-C in the year prior to the start of follow-up.

Participants who die or experience MACE before the start of follow-up will be excluded. Each participant who meets the study eligibility criteria will be entered once for analysis; duplicate entries will be removed.

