#### Sensitivity analyses

To assess the robustness of the primary analyses, the outcomes will be assessed based on earlier lipid test measurements, specifically at 3 months (exposure assessment window days [30, 90]; follow-up window [91, censor]) and 12 months (exposure assessment window [1, 365]; follow-up window [366, censor]) after initiating statin treatment.

The association of LDL-C and non-HDL-C as continuous exposures will be further assessed, rather than as categorical exposures.

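### In the 3-month sensitivity analysis, the two-further-prescriptions entry rule selects patients on up to 275 days of their own follow-up

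*Protocol article*

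**What the plan says.** Protocol article, Eligibility criteria, opens with: "To be included in the study, each patient must meet the following eligibility criteria". One item on the list is: "Have at least two additional statin prescriptions 1 year following index date". Day 0 is fixed under Study design: "The cohort entry date (index date) is defined as the first dispensing or prescribing of a statin between 1 January 2007 and 31 December 2012".

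The start of follow-up differs by analysis:

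- Primary analysis (Outcomes and follow-up): "Follow-up will begin after the end of the exposure assessment window (24 months after prescribing or dispensing of the first statin prescription".
- 12-month sensitivity analysis (Sensitivity analyses): "12 months (exposure assessment window [1, 365]; follow-up window [366, censor".
- 3-month sensitivity analysis (same section): "specifically at 3 months (exposure assessment window days [30, 90]; follow-up window [91, censor".

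Two other entry conditions move with the start of follow-up. The lipid-test criterion reads "Have at least one documented follow-up lipid test for TC, HDL-C, and LDL-C in the year prior to the start of follow-up", and the exclusion for earlier death or MACE is also tied to that start. The prescription rule is the one post-index condition anchored to the index date. The Sensitivity analyses section does not alter it.

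**The concern.** An entry criterion should be decidable on the day risk time begins. In the 3-month analysis this one is not. Two problems follow.

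1. **Immortal time.** A patient who qualifies through a prescription after day 90 was bound to be alive until that prescription. The matching patient who died first is removed, and so is the death. All-cause mortality is a secondary outcome and cardiovascular death is part of MACE, so the loss falls on named outcomes.
2. **Entry that depends on the outcome.** A patient who stopped early and is put back on a statin after a non-fatal MACE can reach the count because of that event. The same patient without an event stays out.

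The 3-month analysis is meant to test whether the primary result is robust to the timing of the lipid test. The Study design section chooses a new-user design in order to avoid survival bias, and this analysis lets a form of it back in. If supply lengths differ between Hong Kong, New Zealand and the UK, the loss differs too. It could then appear as a difference between sites in early event rates.

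**Working it through.** **The plan's own figure.** Feasibility assessment and sample size expects 140 000 CDARS patients, at least 3 years of follow-up and 10 MACE per 1000 person-years: 140 000 × 3 × 0.010 = 4200 events, as stated. The point here does not touch that figure.

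**Overlap of the prescription window with follow-up.** I read the rule as covering days 1 to 365 after index.

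| Analysis | First day of follow-up | Overlap with days 1–365 |
|---|---|---|
| 3-month | 91 | 365 − 91 + 1 = 275 days |
| 12-month | 366 | 0 |
| 24-month (primary) | after 24 months | 0 |

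The 275 days are a maximum. For a given patient the dependence ends at the second additional prescription.

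**Who is affected.** With equal spacing of d days (an assumption; the document gives no intervals), the second additional prescription falls on day 2d. It falls by day 90 only if d ≤ 45. For d = 84, 90 and 120 it falls on days 168, 180 and 240.

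**Events at issue.** At the protocol's rate, MACE risk over the overlap is 1 − exp(−0.010 × 275/365.25) = 0.75%, or about 1050 events per 140 000 patients. If 10%, 25% or 50% of patients are still short at day 90 (assumed shares), about 105, 263 or 525 of those events fall in patients whose inclusion is undecided. These are upper bounds on lost events, because some patients fill the prescriptions before their event.

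**Loss of early deaths.** Assume 25% of MACE are fatal and non-cardiovascular death runs at 8 per 1000 person-years. True mortality is then 0.25 × 10 + 8 = 10.5 per 1000. With equal spacing, the share of the 275 days in which a death causes exclusion is (2d − 90)/275 for d above 45:

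- d = 30: no loss, 10.5.
- d = 90: 90/275 = 0.327, and 10.5 × (1 − 0.327) = 7.1.
- d = 170: 250/275 = 0.909, and 10.5 × (1 − 0.909) = about 1.0.

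Simulations with the same rates, which also include stopping and restarting, gave 6.8 to 7.1 at 90 days, 0.9 to 1.2 at 170 days and almost no change at 30 days.

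**Comparison between LDL-C groups, under a true null.** The simulations used 4 million patients per scenario. They assumed that 10–25% stop after the first prescription, that 60–70% of stoppers and 35% of continuers are in the high LDL-C group, that 50–80% restart after a non-fatal MACE, and spacing of 30–170 days.

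- Over about 6.5 years of follow-up, the low-versus-high MACE ratio was 0.97 to 1.00 (0.98 in the base case). With no restart effect it was 0.998.
- Within days 91–365 alone it was 0.77 to 0.95. Separate runs under narrower assumptions gave 0.88 to 0.96, and 0.93 rather than 0.77 at 170-day spacing. With no restart effect these runs gave 0.98 to 1.01.
- The low-versus-high mortality ratio stayed at 0.99 to 1.02, even at 170-day spacing.

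**The case against.** The strongest reply is that the planned 3-month estimate runs from day 91 to censoring, not to day 365. Over that span the illustrative null ratio moves by at most about 3%, against a planned hazard ratio of 0.85. This stands.

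A reader might infer from the overlap that the 3-month analysis could by itself produce a spurious lower-is-better result. The document does not support that. The larger distortions (0.77 to 0.95) belong to a window the plan never analyses alone. They also rest almost wholly on the restart assumption, and neither stopping nor restart rates are given. Nor does the large fall in early mortality imply a distorted contrast: the loss of deaths lowers the rates in both LDL-C groups and left their ratio near 1.

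A second reply is that the common analysis protocol promised under Data cleaning and validation, which is not shown, may re-anchor eligibility for each sensitivity cohort. It may. But the article states the rule for every patient, gives explicit windows and makes no exception. As written, the two statements produce the problem when followed, so this is more than missing detail.

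**Conclusion.** The point holds for the 3-month sensitivity analysis only. Entry there depends on up to 275 days of follow-up, and this follows from the text without assumptions beyond reading the rule as days 1 to 365.

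That early all-cause and cardiovascular mortality is understated requires only that some patients have prescription intervals above about 45 days. How much is lost depends on those intervals, which are not given and may differ between databases.

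The effect on the hazard ratio between LDL-C groups over full follow-up is probably small, about 0.97 to 1.00 under a true null. That range rests on assumed stopping, restart and spacing figures, and the direction cannot be fixed from the document. A reader should not extend the point to the primary or 12-month results, where the overlap is zero.

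**What to change.** Add a general statement to Sensitivity analyses that no entry criterion may use data after the analysis-specific start of follow-up. For the 3-month analysis, choose one of two routes:

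- drop the additional-prescription rule; or
- keep it, start each patient's risk time at the later of day 91 and the date of the second additional prescription, and exclude patients with MACE or death before that date. This deals with both the immortal time and the patients who qualify because of an event.

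Do not instead require two further prescriptions by day 90. With intervals above 45 days the second falls after day 90, so this would remove nearly all patients on longer supplies and tie the sample to local supply length.

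The cost is a sentence or two. Dropping the rule admits some one-prescription users, so the 3-month cohort then differs from the primary one in population as well as in timing. Delayed entry gives up some early person-time; at 90-day spacing, for example, entry moves from day 91 to day 180. The primary and 12-month analyses need no change.
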